#### Analysis of secondary outcome measures

The distribution of TRAb titres will be compared between patients in and out of remission by graphical summary, numerical summary statistics (median and IQR) and a Mann-Whitney test.Time to recovery of peripheral blood B cell lymphocyte numbers (CD19+ cells) to above 70% of the patient’s pre-RTX level in relation to thyroid hormone status. This will be compared between patients in and out of remission by graphical summary, numerical summary statistics (median and IQR) and a Mann-Whitney test.Cumulative dose of ATD (CBZ) in mg/kg in relation to thyroid hormone status. This will be compared between patients in and out of remission by graphical summary, numerical summary statistics (median and IQR) and a Mann-Whitney test.We will assess the time taken for TSH concentrations to normalise (increase above 0.1mU/L) post-RTX and describe biochemical thyroid status, as assessed by TSH, FT4 and FT3 concentration, in the period between cessation of ATD therapy at the end of year 1 and the end of the trial. Specifically we will plot the time taken for TSH to normalise in individual patients and determine the proportion of time that TSH, FT4 and FT3 concentrations are within the normal reference range in the period between ATD stopping (end of year 1) and trial end (end of year 2).The frequency and nature of adverse events.

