## Methods and analysis

### Trial objectives

The primary objective is to establish whether a single 500 mg dose of RTX, when administered together with a 12-month course of ATD, is likely to result in a meaningful improvement in the proportion of young people with Graves’ hyperthyroidism entering disease remission.

The secondary objectives are to examine (1) the relationship between thyrotropin receptor antibody (TRAb) titre and thyroid hormone status (thyroid stimulating hormone [TSH], free thyroxine [FT4] and free tri-iodothyronine [FT3]) in recruited subjects at the beginning and end of the trial; (2) whether immune cellular response is related to disease outcome by examining the relationship between time to recovery of B cell numbers measured in peripheral blood to within the local normal reference range and thyroid hormone status at the end of the trial; (3) whether total dose of ATD is related to disease outcome; (4) the time taken for TSH concentrations to normalise post-RTX and to describe thyroid status, as assessed by TSH, FT4 and FT3 concentrations (normal or abnormal), in the period between cessation of ATD therapy and the end of the trial in each patient; and (5) the safety of the trial treatment regimen by determining the nature and frequency of adverse events.

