### ATD therapy (CBZ and PTU)

A 12-month course of ATD will be administered to induce a euthyroid state in the months following diagnosis. Therapy will normally be with CBZ, which can be administered once daily. PTU is a second-line therapy because of the increased likelihood of hepatic failure with this drug. It is proposed that CBZ dose be titrated against prevailing thyroid function tests in order to maintain a euthyroid state. Clinicians will be encouraged to follow the schedule outlined in table 1 when administering ATD to patients enrolled into this clinical trial, although the managing clinician can elect not to follow the above framework if their assessment of the overall clinical picture suggests that this is in the patients’ best interests. PTU can be administered on the basis that 5 mg of CBZ is equivalent to 50 mg PTU. If patients become hypothyroid (with an elevated TSH and low FT4/FT3 level) on the smallest daily dose of CBZ (5 mg) or PTU (50 mg), then the ATD can be administered on alternate days. If patients are still hypothyroid, then the ATD will be stopped before 12 months has elapsed following RTX therapy.

**Table 1 T1:** CBZ dose adjustment according to changing thyroid hormone status

Week/stage of trial	Thyroid hormone level: FT4 and FT3 (pmol/L)	CBZ dose (mg)
Presentation		20 mg CBZ once daily (consider 10 mg in the case of mild hyperthyroidism, FT3<10).
Week 4	Biochemically hypothyroid (low FT4, FT3 not raised).	Reduce to 5 mg.
	FT3 normal and FT4 falling.	Consider reducing from 20 mg to 10 mg, or from 10 to 5 mg.
	FT3 elevated.	Continue prior dose.
Week 8	Biochemically hypothyroid (low FT4, FT3 not raised).	Reduce to 20 mg, 10 mg, 5 mg, or reduce CBZ to 5 mg alternate days.
	FT3 normal and FT4 falling.	Reduce from 20 mg to 10 mg, from 10 mg to 5 mg, or remain on 5 mg.
	FT3 elevated but improving.	Continue prior dose.
	FT3 raised or increasing further.	Consider increasing CBZ by 10 mg daily.
Week 12 and beyond	Biochemically hypothyroid (low FT4, FT3 not raised).	Reduce to 10 mg, 5 mg or reduce CBZ to 5 mg alternate days.
	FT3 normal (or elevated with low FT4).	Continue current dose.
	FT3 elevated.	Consider increasing CBZ by 10 mg daily or 5 mg daily if previously euthyroid.
Week 16 and beyond	TSH elevation (>4 mU/L) (TSH takes precedence over thyroid hormone levels).	Reduce CBZ dose by 5–10 mg daily.
	TSH still suppressed.	Follow guide above for week 12.

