CBZ, carbimazole; FT3, free tri-iodothyronine; FT4, free thyroxine; TSH, thyroid stimulating hormone.

Any participants who develop unacceptable toxicity to CBZ (notably neutropaenia with a neutrophil count less than 0.5×10^9^/L) will stop ATD immediately. Participants with a neutrophil count between 0.5 and 1.0 can remain on ATD if well. The neutrophil count should be repeated after approximately 1–2 weeks or as clinically indicated to confirm that it has not fallen to less than 0.5×10^9^/L. PTU can be commenced as a replacement ATD in the case of adverse events that do not involve hepatic dysfunction or neutropaenia. The increased risk of liver dysfunction on PTU will be discussed with participants and their families prior to commencing PTU. Patients on PTU will have liver function checked at each visit and PTU stopped if ALT or bilirubin is elevated (2× above the upper limit of normal). If patients are unable to tolerate ATD, then it may be feasible to monitor patients off treatment or manage them symptomatically with beta blockade on the basis that RTX may alter the disease natural history and result in remission without further ATD. This option can be discussed with the participant/the participant and their family. Other potential means of maintaining a euthyroid state can be discussed with the trial management team.

Patients who relapse in the second year of the trial will be encouraged to return to ATD in the first instance.

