### Outcome measures

#### Primary

The number of subjects in remission at 2 years following a single dose of RTX and a 12-month course of ATD is the primary trial endpoint: this is equivalent to the number who have not relapsed. Subjects will be deemed to have relapsed if they are receiving any concomitant ATD medication in the second year post-RTX administration, or have undergone surgical (thyroidectomy) or RI treatment because of hyperthyroidism at any time following RTX administration. They will also be deemed to have relapsed if serum TSH is less than the lower limit of the normal laboratory reference range and serum FT3 is above the upper limit of the normal laboratory reference range at 2 years.

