#### Secondary

TRAb titre and related thyroid hormone status at the time of RTX administration and 2 years post-RTX.Time to recovery of B cell lymphocyte numbers in peripheral blood to the normal local lab reference range in relation to thyroid hormone status.Cumulative dose of ATD (mg/kg) in relation to thyroid hormone status 2 years post-RTX.Time taken for TSH and thyroid hormone concentrations to normalise to within the local laboratory reference range post-RTX, and describe biochemical thyroid status in the period between cessation of ATD and 2 years post-RTX in each patient.The frequency and nature of adverse events.

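### Year-2 time in normal range pools values on rescue treatment with off-drug values and starts at a fixed date that the protocol contradicts elsewhere; the cumulative antithyroid-drug dose has no stated end

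*Protocol article*

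**What the plan says.** All references are to the protocol article.

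- **Time in range (Analysis of secondary outcome measures).** The plan is to "determine the proportion of time that TSH, FT4 and FT3 concentrations are within the normal reference range in the period between ATD stopping" and the end of the trial. The paragraph twice places the stop at the end of year 1. It does not mention restarted ATD, radioiodine or thyroidectomy.
- **Same item elsewhere.** Trial objectives (item 4) and Outcome measures, Secondary, both describe thyroid status from cessation of ATD in each patient.
- **Early stops.** For patients who remain hypothyroid on alternate-day dosing, "then the ATD will be stopped before 12 months has elapsed following RTX therapy" (ATD therapy). The Introduction also provides for stopping before 12 months, and the ATD therapy section stops the drug at once for unacceptable toxicity.
- **Rescue.** "Patients who relapse in the second year of the trial will be encouraged to return to ATD in the first instance" (ATD therapy).
- **Primary endpoint.** "Subjects will be deemed to have relapsed if they are receiving any concomitant ATD medication in the second year post-RTX administration". Thyroidectomy or radioiodine for hyperthyroidism at any time after rituximab also counts as relapse.
- **Cumulative dose.** The objective is "whether total dose of ATD is related to disease outcome". The outcome is "Cumulative dose of ATD (mg/kg) in relation to thyroid hormone status 2 years post-RTX". The analysis is "Cumulative dose of ATD (CBZ) in mg/kg in relation to thyroid hormone status", compared between patients in and out of remission with a Mann-Whitney test. None of the three says when accumulation ends.

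**The concern.** The time-in-range summary is the trial's description of thyroid status after the planned course has ended. Its value lies in showing how patients do off drug. With the window running to trial end whatever happens, a relapser whose hormones are brought back to normal by restarted ATD, or by replacement after surgery or radioiodine, collects in-range time just as a patient in drug-free remission does. Most patients may be affected, because the design itself expects 20% to 40% to remit.

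The fixed start adds a second fault. For a patient who stops early, it discards off-drug time that the objective asks for.

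The dose comparison carries a related risk. Year-2 ATD is part of the definition of relapse, so it cannot also enter the exposure compared between remitters and relapsers without building in a difference.

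**Working it through.** **1. The design figure, to size the groups.** Inputs from Sample size: 20% unacceptable and 40% desired remission, alpha 10%, beta 20%, 10% loss. The smallest exact-binomial design is n = 24 with critical number 8 (alpha 0.089, power 0.808). 24/0.9 = 26.7, rounded up to 27, which matches the stated target. Among 24 evaluable patients the non-remitters would number 24 × 0.6 = 14.4 to 24 × 0.8 = 19.2, so about 14 to 19. This point does not change the target.

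**2. Time in range by visit.** Table 2 has four visits after week 52: weeks 65, 78, 91 and 104. Take a patient found abnormal and restarted at week 65. The time to control is an assumption:

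| Controlled by | Normal visits after week 52 | Of these, off drug |
|---|---|---|
| week 78 | 3 of 4 | 0 |
| week 91 | 2 of 4 | 0 |
| week 104 | 1 of 4 | 0 |

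**3. Time in range by month.** Assume ATD stops at month 12, values are normal until relapse t months later, ATD restarts at relapse, and control takes L months. As written, in-range time is t + (12 − t − L) = 12 − L months of 12. If nothing from relapse onward is credited, it is t of 12.

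| t | L | As written | Not credited from relapse |
|---|---|---|---|
| 1.5 | 2 | 10/12 = 83% | 12.5% |
| 3 | 2 | 10/12 = 83% | 25% |
| 3 | 3 | 9/12 = 75% | 25% |
| 6 | 3 | 9/12 = 75% | 50% |

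Under these assumptions t cancels out of the first formula. The measure as written then reflects how quickly rescue works and not how long the patient stayed well off drug.

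**4. Start of the window.** Suppose a patient stops ATD at the week 36 visit. From actual cessation to trial end is 104 − 36 = 68 weeks. From the end of year 1 it is 104 − 52 = 52 weeks. The two definitions differ by 16 weeks of off-drug time.

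**5. Cumulative dose, if year-2 ATD were included.** By the primary definition, remitters have zero year-2 ATD. The illustration uses 24 patients and year-1 dose unrelated to outcome. None of the following comes from the documents:

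- year-1 dose: mean 12 mg/day, coefficient of variation 0.5
- weight: mean 55 kg, SD 10
- 90% of non-remitters restart at a uniform time in year 2 and continue to trial end
- 2,000 simulated trials per cell, two-sided Mann-Whitney test at 5%

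| Remission rate | Year-1 dose only | + rescue 5 mg/day | + 10 mg/day | + 20 mg/day |
|---|---|---|---|---|
| 20% | 4-5% | 12% | 26% | 53% |
| 30% | 4-5% | 12% | 30% | 64% |
| 40% | 4-6% | 15% | 35% | 71% |

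The year-1 column gives the spread over the three runs at each remission rate. The rescue doses are inputs to the illustration only.

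**The case against.** **The time-in-range analysis is descriptive.** It has no test and no planned comparison of remitters with relapsers, and nothing in the article calls in-range time recovery. The primary endpoint already treats "receiving any concomitant ATD medication in the second year post-RTX administration" as relapse. This stands, and it limits the consequence: the decision to proceed to a further trial is untouched. A description that cannot separate drug-produced normal values from off-drug ones still does not answer its own objective.

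**A normal value is a normal value.** Scoring biochemically normal results as out of range would misreport them. This also stands, and it is why the fix separates the time instead of rescoring it.

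**Detail belongs in the analysis plan, and end of year 1 is only shorthand.** An article may leave detail out. Here, however, two different starting points are both stated, and the fixed one appears twice in its paragraph. That is a contradiction to resolve, even if few patients stop early.

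**Control by week 78 is optimistic.** Table 1 allows for TSH still being suppressed at week 16 and beyond. This is fair, and the range in the working covers slower control.

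**Cumulative dose.** A reader might infer that restarted ATD is counted and that the dose comparison is therefore circular as planned. The document does not support that. No section says year-2 ATD enters the total. The trial course is consistently described as 12 months, the telephone calls on dose changes cover the first 12 months, and the ATD regimen and compliance rows of Table 2 end at week 52. Concomitant medication is recorded to week 104, so inclusion remains possible but is not stated.

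**Conclusion.** The time-in-range point holds on the text. Following the rule as written pools on-rescue and off-drug normal values in a sample where about 14 to 19 of 24 evaluable patients may be non-remitters at the design rates. For one relapser with the assumed course of month-3 relapse and control in 2 to 3 months, the reported figure is 75-83% of year 2, against 25% if time from relapse is not credited. Those percentages depend on the assumed timings; the pooling does not. The fixed start contradicts the objectives, the secondary outcome and the early-stop provisions, and these must be reconciled.

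The dose point is conditional. The window is unstated. If year-2 ATD is included, the comparison is circular, with an illustrative false-positive rate of about 12-71% depending on assumed rescue dose and remission rate. If accumulation ends at 12 months the mechanism is absent, and the rate is about 5%.

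Both matters are secondary. Neither affects the primary endpoint, the critical number or the sample size.

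**What to change.** In the analysis section (or the analysis plan):

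1. Start the time-in-range window at each patient's actual ATD stop, in line with the objectives and secondary outcome.
2. End the off-treatment measure at the first of ATD restart, radioiodine or thyroidectomy, and report time after that separately as status on or after rescue.
3. Show the length of each patient's off-treatment period beside the proportion. Once the clock stops, a patient who is normal for 3 months and then restarts scores 3/3 = 100% of a short period, which would mislead if given alone.
4. State that cumulative ATD dose ends at the planned 12-month stop or the earlier actual stop.
5. Convert propylthiouracil (PTU) with the protocol's own equivalence (5 mg carbimazole, CBZ, to 50 mg PTU). The analysis line names only CBZ, while the outcome is defined for ATD.

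The cost is wording. Table 2 already schedules the ATD regimen to week 52, and concomitant medication and thyroid function to week 104. Radioiodine and thyroidectomy must be recorded for the primary endpoint in any case. Clinical management is unchanged.

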### Inclusion criteria

Excess thyroid hormone concentrations at diagnosis: elevated free FT3 and/or FT4 (based on local assay).Suppressed (unrecordable) TSH (based on local assay).Patients between the ages of 12 and 20 years inclusive who are less than 6 weeks from the initiation of ATD treatment (CBZ or propylthiouracil [PTU]) for the first time.Elevated thyroid binding inhibitory immunoglobulin or thyroid receptor antibodies (TRAb including thyroid binding inhibiting immunoglobulin [TBII]) based on local assay. Patients may or may not have a raised thyroid peroxidase antibody titre.All patients must be willing to use effective forms of contraception for 12 months post-treatment with RTX.If women are of childbearing potential, they must have a negative pregnancy test at screening. This will need to be repeated on the day of RTX administration if more than 7 days has elapsed since the screening visit or a negative pregnancy test.Able and willing to adhere to a 2-year trial period.

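### The analysis of secondary outcome 4 starts the off-ATD period at the end of year 1, whereas the objective starts it at each patient's own ATD stop

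*Protocol article*

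**What the plan says.** All references are to the Protocol article.

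- **Trial objectives**, secondary objective 4: thyroid status is to be described "in the period between cessation of ATD therapy and the end of the trial in each patient". The matching item under Outcome measures, Secondary, is likewise defined patient by patient, from ATD cessation to 2 years after rituximab (RTX).
- **Analysis of secondary outcome measures**, fourth item: ATD cessation is placed at the end of year 1 twice. The second time it fixes the denominator of a computed quantity, the proportion of time that TSH, FT4 and FT3 are in the reference range "in the period between ATD stopping (end of year 1) and trial end (end of year 2".
- **ATD therapy (CBZ and PTU)**: for a patient who remains hypothyroid on alternate-day dosing, "then the ATD will be stopped before 12 months has elapsed following RTX therapy". The Introduction also provides for an early stop for hypothyroidism. The ATD therapy section adds an immediate stop for unacceptable toxicity and allows for monitoring a patient off treatment.
- **Table 2** and the text below it: TSH, FT4 and FT3 are measured at every visit from week 0 to week 104. ATD changes in the first 12 months are recorded at visits and by telephone.

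**The concern.** The objective and the outcome list define one window and the analysis section defines another. They coincide only for patients who take ATD for the full year after RTX. For a patient who stops earlier, a programmer following the analysis section would start at week 52 and ignore the first drug-free months. A programmer following the objective would include them.

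This matters because those months are what the outcome sets out to describe, and the primary endpoint does not fully cover them. Under the primary definition, ATD use counts as relapse only in the second year, biochemical relapse is judged only at 2 years, and only thyroidectomy or radioiodine counts at any time after RTX. Take a patient who stops ATD early, becomes biochemically hyperthyroid off drug in year 1, and is off ATD and in range from the start of year 2. That patient is not a relapse. Secondary outcome 4 is where the episode would be described, and a fixed week-52 start omits it.

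**Working it through.** **The plan's own figure.** The protocol gives no number for this outcome. Its one computed figure, the target of 27, reproduces. With remission rates of 20% and 40%, one-sided alpha of at most 10% and power of at least 80%, the smallest exact single-stage design is 24 patients with at least 8 remissions (alpha 0.0892, power 0.8081). Allowing for 10% loss, 24 / 0.9 = 26.7, rounded up to 27. Nothing in this point changes that.

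**Inputs.** The end of year 1 is taken as week 52 and the end of trial as week 104 (Table 2). Scheduled thyroid tests between week 20 and week 52 fall at weeks 20, 28, 36, 44 and 52 (Table 2). The stop week *s* is an assumption, set at scheduled visits, because the protocol gives no distribution of early stops.

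**Formulas.**
- Off-drug weeks under the objective: 104 − *s*
- Off-drug weeks under the analysis text: 104 − 52 = 52
- Weeks left out: 52 − *s*
- Share left out: (52 − *s*) / (104 − *s*)

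| Assumed stop (week) | Off-drug weeks | Left out | Share | Scheduled tests after the stop and before week 52 |
|---|---|---|---|---|
| 20 | 84 | 32 | 38% | 28, 36, 44 |
| 28 | 76 | 24 | 32% | 36, 44 |
| 36 | 68 | 16 | 24% | 44 |
| 44 | 60 | 8 | 13% | none |
| 52 | 52 | 0 | 0% | none |

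**Effect on one patient's result (illustration).** Assume a stop at week 28, no restart, and in-range values for half of year 2 (26 of 52 weeks).
- Under the analysis text: 26 / 52 = 50%.
- From the patient's own stop, out of range throughout weeks 28 to 52: 26 / 76 = 34%.
- From the patient's own stop, in range throughout weeks 28 to 52: (26 + 24) / 76 = 66%.

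For this patient the reported proportion could be 16 percentage points too high or too low, depending on the months left out.

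**Starting point for time to normalisation.** This is a separate question about the same outcome. The objective times "the time taken for TSH concentrations to normalise post-RTX", and the outcome list and the analysis section also count from RTX, so there is no conflict over the origin. Patients may enter when "less than 6 weeks from the initiation of ATD treatment (CBZ or propylthiouracil [PTU]) for the first time", so the interval from first ATD dose to RTX varies from 0 to just under 6 weeks. This takes the criterion as applied at week 0, where Table 2 repeats the eligibility check.

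**The case against.** **The parenthesis may be shorthand.** The analysis section still defines the period by ATD stopping, and the end of year 1 is when the planned 12-month course ends. On that reading nothing is excluded. The reading is fair, and it may be what the authors meant. But the end of year 1 appears twice, once inside the definition of a denominator, and the same protocol provides for earlier stops. If it is shorthand, removing it loses nothing.

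**The data are not lost.** This stands. Thyroid function is measured and ATD changes are recorded throughout year 1, and surgery or radioiodine at any time already counts as relapse. The gap is in what the summary covers, not in what is collected.

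**The size is hypothetical.** This also stands. The number and timing of early stoppers are not given. Hypothyroid patients go to alternate-day dosing before stopping, and some patients with toxicity may switch to PTU, which is still ATD.

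**A stronger reading a reader might infer** is that counting time to normalisation from RTX is itself wrong, because earlier ATD treatment shortens it. The documents do not support that. RTX is the declared origin throughout. Table 1 lists dose actions for alternative week-4 results, including an elevated FT3, and does not predict normal values by then. The analysis section times TSH, which must be suppressed for eligibility and which Table 1 still allows to be suppressed at week 16 and beyond; only the outcome list adds thyroid hormones. Moving the origin to the first ATD dose would change the objective. No thyroid function test is scheduled before week 0, so a patient already normal by then would have no scheduled date of normalisation.

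**Conclusion.** The off-ATD window is inconsistent within the protocol and should be reconciled. The objective and the outcome list run it from each patient's own ATD stop; the analysis section fixes it at the end of year 1. Read literally, the analysis section leaves out 13% to 38% of an early stopper's off-drug time for assumed stops between weeks 44 and 20, and 32% for a stop at week 28. These are figures per affected patient, and the effect across the trial is unknown.

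The consequence is limited to a descriptive secondary outcome. The primary endpoint, the sample size and the decision to proceed do not depend on it. Timing normalisation from RTX is not an error. The varying ATD lead-in of 0 to under 6 weeks only makes that result harder to interpret without context.

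**What to change.** In the fourth item of Analysis of secondary outcome measures:

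1. Start the off-ATD window at each patient's actual ATD stop date, as the objective and the outcome list already do, and delete both references to the end of year 1.
2. State how a patient who stops and then restarts ATD in year 1 is counted: for example from the first stop with on-drug time removed, or from the last stop. Without this, a window based on each patient's own stop is still ambiguous.

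Optionally, keep RTX as the origin for time to normalisation and report beside it the interval from first ATD dose to RTX and the number of patients whose values are already normal at week 0.

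The cost is a wording change here and in the analysis plan if it repeats the text. ATD regimen and thyroid function are already collected at the scheduled visits, and the ATD start date is already needed for eligibility. No new visits, tests or patients are required.
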